## Abstract

**Background:**

Osteoarthritis is a highly prevalent and disabling condition. In early stages, patients are asymptomatic or only experience activity-related pain. When pain intensifies, the disease has often progressed, with few treatment options besides knee arthroplasty. Recently, there has been a growing interest in acoustic emissions generated by poorly lubricated and/or damaged moving joint surfaces, as seen in osteoarthritis. Noninvasive analysis of knee sound could help identify patients with early-stage osteoarthritis at a low cost, without radiation exposure. Thus, preventive measures could be implemented earlier and delay the progression of osteoarthritis.

**Objective:**

This study aims to identify acoustic biomarkers with prognostic value for the early detection of osteoarthritis. To achieve this, a preliminary reference database will be developed using a subpopulation at risk of developing osteoarthritis, incorporating acoustic signals and gold-standard clinical measures for validation.

**Methods:**

A total of 100 patients with previous reconstructive knee surgery and 20 healthy controls will be examined twice at a 9-month interval for both knees. Acoustic emissions (AE) will be recorded with the Inmodi knee brace (École Polytechnique Fédérale de Lausanne; EPFL) during 4 functional tests (unloaded flexion-extension, sit-to-stand test, one-step test, and walk test). Gold-standard osteoarthritis diagnostics will be assessed and evaluated by an experienced radiologist for (1) the magnetic resonance imaging (MRI) Osteoarthritis Knee Score (MOAKS) and (2) the Kellgren-Lawrence (KL) grading scores. Feature analysis and multivariate modeling will be used to study the association between the extracted sound parameters and osteoarthritis (MOAKS and KL). In addition, thermal images will be taken to investigate the state of inflammation. Participants will fill out 5 health-related questionnaires (Oxford Knee Score [OKS], Core Outcome Measures Index [COMI], University of California at Los Angeles [UCLA ]activity scale, Knee Injury and Osteoarthritis Outcome Score [KOOS], and Forgotten Joint Knee Score-12 [FJS-12]) at both time points.

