### Project Population

This study targets a population at risk of osteoarthritis. The risk of knee osteoarthritis after knee joint injury is up to 5-fold that of noninjured patients. As many as 50% of individuals with an anterior cruciate ligament (ACL) or meniscus tear develop knee osteoarthritis [21]. Therefore, to represent the whole distribution of osteoarthritis stages in the study sample, participants will be recruited from the clinic’s Meniscus/ACL/Cartilage (MAC) surgery registry at 2- and 5-year postoperative times. All patients from the MAC registry will be screened regardless of whether they have undergone isolated meniscal tear repair, isolated ligament reconstruction, or a combined meniscal and ligament procedure. Additionally, a healthy control group and a late-stage osteoarthritis group will also be included. The inclusion and exclusion criteria presented in Textbox 1, follow established standards and are consistent with those used in similar studies (eg, NCT02937064).

The total study sample will be 120 patients in 6 groups:

Group A: 20 healthy participantsGroup B1: 20 patients from the MAC registry at 2 years postoperative with normal outcomes (normal and poor outcomes are defined in section Recruitment)Group B2: 20 patients from the MAC registry at 2 years postoperative with poor outcomesGroup C1: 20 patients from the MAC registry at 5 years postoperative with normal outcomesGroup C2: 20 patients from the MAC registry at 5 years postoperative with poor outcomesGroup D: 20 patients booked for in-house unilateral TKA surgery for severe osteoarthritis

Even if it is not possible to perform an exact power analysis for the ML models to be trained, we can use a simple proxy model to estimate the effect size that we can reasonably expect to detect with a sample size of 120. Thus, if we aim to estimate the differences in KL gradings from the AEs, the smallest detectable correlation with 80% power and a significance level of *P*=.05 would be 0.25. In one-way ANOVA, this corresponds to a minimum explained variance of approximately 7%, which is considered a small-to-medium effect size [22]. Smaller effect sizes are unlikely to be detected within our population.

Textbox 1.Detailed inclusion and exclusion criteria for the groups.

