### Withdrawal and Discontinuation

The patients can withdraw from the study at any point in time. In the declaration of consent, the patient agrees that the data already collected stays in the study. Patients who have knee surgery or a knee injury within the follow-up time or patients who become otherwise severely ill will not be invited for the second visit. In all cases above, the data will be encrypted and used for evaluation. If the enrollment phase is still ongoing, the withdrawn patient will be replaced with a person of the same sex, comparable age, and study group type (A, B1, B2, C1, C2, and D).

If a participant misses the first visit as well as a substitute appointment, the participant will be withdrawn and replaced. If a participant misses the second visit and substitute appointment, his data collected from the first visit will be used.

If a person becomes pregnant, the study will continue but without EOS radiography.

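### The abstract counts 100 post-reconstruction patients where the groups supply 80, and the stated two visits for all 120 conflict with the rule on knee surgery during follow-up

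*Protocol article*

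**What the plan says.** The Methods paragraph of the Abstract gives the sample as "A total of 100 patients with previous reconstructive knee surgery and 20 healthy controls", to be examined twice, nine months apart. Project Design repeats that all 120 participants are seen twice.

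Project Population says "The total study sample will be 120 patients in 6 groups" and lists them, each of size 20. Group A is healthy. B1, B2, C1 and C2 come from the Meniscus/ACL/Cartilage (MAC) surgery registry; B1, for example, is "20 patients from the MAC registry at 2 years postoperative with normal outcomes". Group D is "20 patients booked for in-house unilateral TKA surgery for severe osteoarthritis". The section justifies the registry groups by their raised risk after injury, then introduces the other two as additions: "Additionally, a healthy control group and a late-stage osteoarthritis group will also be included". Textbox 1 asks of Group D only an age range and a booked knee replacement for severe osteoarthritis.

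The same section gives the only detectable-effect figure in the article. It is a proxy calculation meant to "estimate the effect size that we can reasonably expect to detect with a sample size of 120", and it puts "the smallest detectable correlation with 80% power" at 0.25.

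Withdrawal and Discontinuation states that "Patients who have knee surgery or a knee injury within the follow-up time" will not be invited to the second visit, and that data already collected from them are kept and used.

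**The concern.** Two statements about sample size do not match the design described in the body of the article.

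First, the abstract presents every participant who is not a control as a patient after reconstructive surgery. A fifth of those 100 are end-stage patients recruited on a different basis, and the abstract never mentions them. The objective is early detection in a subpopulation at risk. A discrimination or correlation estimate from a sample that contains both healthy controls and patients awaiting knee replacement may look different from one within the at-risk patients, so readers need to know who is in the sample.

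Second, Group D enters the study because knee surgery is scheduled, and knee surgery during follow-up removes the second-visit invitation. No exception for Group D is stated. The size of the longitudinal dataset, which serves the analysis of change and the secondary aim on progression, is then not the 120 given in the Abstract and Project Design.

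**Working it through.** **Group counts (Project Population; Table 3 confirms 20 per group)**

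- Registry patients after surgery: B1 + B2 + C1 + C2 = 4 × 20 = 80
- Awaiting knee replacement: D = 20
- Healthy: A = 20
- Total: 80 + 20 + 20 = 120

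The abstract's 100 + 20 = 120 has the same total. Its 100 equals 80 + 20, that is, registry patients plus Group D. The post-reconstruction count is (100 − 80)/100 = 20% lower than stated.

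**Two-visit count**

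The article gives no operation dates. Let d be the number of Group D patients operated on before their second visit, with d from 0 to 20. The largest possible two-visit set is 120 − d, so between 120 and 100, before any other dropout.

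**The plan's own detectable correlation**

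Inputs: n = 120, 80% power and significance level .05, all from Project Population. The article does not state sidedness or the number of observations per participant; I assume a two-sided test and one observation each.

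Fisher z: r = tanh[(1.960 + 0.842)/√(n − 3)]

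- n = 120: tanh(2.802/√117) = tanh(0.259) = 0.253

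As a cross-check, the noncentral t test of a correlation, with noncentrality r√n/√(1 − r²) and n − 2 degrees of freedom, gives 0.250. The stated 0.25 is reproduced. A one-sided test would give 0.226, so two-sided is the reading that fits.

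**The same calculation in the smaller sets**

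| Set | n | Detectable r, Fisher z | Detectable r, noncentral t | Power at r = 0.25 (Fisher z; noncentral t) |
|---|---|---|---|---|
| All groups, visit 1 | 120 | 0.253 | 0.250 | 79%; 80% |
| Two-visit set if all of D are operated on | 100 | 0.277 | 0.272 | 71%; 72% |
| Registry patients only | 80 | 0.309 | 0.302 | 61%; 63% |

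Fisher z power is Φ[atanh(0.25)·√(n − 3) − 1.960]. At n = 80 this is Φ(0.2554 × 8.775 − 1.960) = Φ(0.281) = 0.61.

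**The case against.** The strongest reply is that this is one mislabelled sentence in an abstract. The body describes the six groups consistently, all 120 were enrolled, Table 3 shows 20 in each, and no estimate changes. The study is exploratory, its size was set by feasibility, and spanning the whole range of disease stages is a declared design choice. Much of this stands: there is no recruitment shortfall, and including Groups A and D is not an error.

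A reader might infer that the miscount undermines the detectable correlation of 0.25. It does not. The article ties that figure to 120, it reproduces at 120, and the total is 120 under either description. Nor does the article claim 0.25 for the at-risk patients; the figure appears directly after the group list that identifies Group D. What remains is a matter of scope. The section opens by naming an at-risk target population and closes the power paragraph by referring to what can be detected in the study's population, so the set to which 0.25 applies is worth stating.

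It can also be said that the subset figures rest on one observation per participant, although both knees are measured and repeated-measures correlations are planned. That is fair, and the figures should carry that assumption. The follow-up rule is a separate matter from the count, but it contradicts the same abstract sentence, so both are best corrected together. Keeping the first-visit data of operated patients preserves the cross-sectional set but does not supply a second visit.

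**Conclusion.** The point holds as an inconsistency in the stated sample, in two parts. The post-reconstruction sample is 80, not 100. The claim that all 120 are examined twice cannot be squared with the withdrawal rule unless no Group D patient is operated on before the second visit or Group D is exempt, and the article says neither. The two-visit set lies between 100 and 120 before other dropout. It would be too strong to say that Group D is lost to follow-up as a whole, because operation dates are not given.

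The 0.25 is correct for all 120 at visit 1. The values of about 0.27 to 0.28 (n = 100) and 0.30 to 0.31 (n = 80) show only what analyses of those subsets could detect, for a single two-sided test at .05 with one observation per participant. They do not correct the plan's figure.

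**What to change.** 1. Reword the abstract to 80 patients after reconstructive knee surgery, 20 patients booked for knee replacement for severe osteoarthritis, and 20 healthy controls.
2. Reconcile the two-visit statements in the Abstract and Project Design with Withdrawal and Discontinuation, say how Group D is treated under that rule, and state the expected n for the longitudinal dataset.
3. State that 0.25 refers to all 120 at visit 1. Add, with the assumptions of a two-sided test and one observation per participant, that the figure is about 0.30 to 0.31 for the 80 at-risk patients and about 0.27 to 0.28 if only 100 have two visits.
4. Report early-osteoarthritis performance in the 80 at-risk patients alongside the full-sample result.

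Items 1 to 3 cost wording only. Item 4 is one further analysis of data already being collected. The price is a less favourable stated figure and wider intervals for the subset.

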**Results:**

Recruitment and data collection started in December 2022. In November 2023, data collection of all 120 participants (female: n=49, 41%) was completed for the first visit. The data collection for the second visit will end in 2024. Preliminary data processing and analysis are ongoing at the time of this writing.

**Conclusions:**

This exploratory study will contribute to a better understanding of the disease progression of osteoarthritis and the use of acoustic biomarkers for predicting osteoarthritis.

## Introduction

### Disease Background

Osteoarthritis is a highly prevalent and disabling condition that affects over 7% of people globally (528 million people) [1]. It is significantly limiting their mobility and independent lifestyle. Osteoarthritis is mainly characterized by loss of cartilage, structural changes in bone, and inflammation of the synovium and joint capsule. Common risk factors include aging, obesity, prior joint injury, and repetitive joint stress increasing local joint wear. Osteoarthritis takes several years to develop before the patient sees the doctor when the pain intensifies. In the early stages, patients are asymptomatic or only experience activity-related pain. The pain becomes constant over time with intermittent intense pain episodes. The average annual cost of osteoarthritis for an individual is estimated to be between US $700-$15,600 worldwide (2019) [1]. Consequently, osteoarthritis has a large socioeconomic impact due to its associated high medical cost expenditures, as well as indirect costs, such as early retirement and high absenteeism from work.

Osteoarthritis typically affects the hips, knees, hands, feet, and spine, with a high prevalence of polyarticular involvement. This study focuses on knee osteoarthritis.

### Contemporary Standard of Assessment

The contemporary gold-standard assessment of the severity of knee osteoarthritis is based on plain radiography, using the Kellgren-Lawrence (KL) grading system, which was accepted as a standard by the World Health Organization in 1961 [2]. This system does not evaluate the primary affected tissue—cartilage—but only the overall aspect of the joint. It is, therefore, unable to detect early stages of osteoarthritis, and the diagnosis is often established at a late stage, limiting the number of treatment options and typically leading to knee replacement surgery.

### Alternative Assessment Methods

Earlier diagnosis and improved patient stratification are required to deploy preventive osteoarthritis treatments. Possible early diagnostic options include magnetic resonance imaging (MRI) and biochemical markers. MRI can be used to assess changes in cartilage volume, thickness, or even quality [3]. However, the use of MRI is limited by its high cost, availability, and the absence of a validated international score [4]. Alternative clinical imaging modalities have also been proposed to address the shortcomings of KL at the time of writing this, such as ultrasound [5] or computed tomography [6]; however, their use remains relatively limited compared to X-rays. Many biochemical markers are under investigation, but so far, they lack specificity to joint tissues and to particular joints, and sensitivity and specificity are still not high enough for widespread clinical use [7]. Recently, there has been a growing interest in acoustic analysis as an alternative to conventional biomarkers, particularly for the knee joint. The assumption is that the affected joint will generate abnormal acoustic events during motion due to poor lubrication or surface damage and that acoustic analysis will detect and quantify these abnormal events as a measure of joint damage [8-17].

### Relevance of the Project

A wearable device was developed at the École Polytechnique Fédérale de Lausanne (EPFL) for collecting and processing acoustic and kinematic signals. This device—called the Inmodi knee brace—collects airborne acoustic data from the medial and lateral subpatellar areas and kinematic information from the thigh and the calf, both modalities synchronously [17,18]. The platform is then complemented by thermal information of the knee as a measure of inflammation and uses artificial intelligence–based data analysis to extract and combine relevant biomarkers of joint function from each modality. Preliminary data suggests that this combined approach may enable a noninvasive early diagnosis of osteoarthritis. A preliminary *in vitro* animal study with horses’ legs showed a strong association between the joint condition and the power of acoustic emission (AE) signals analyzed [19]. Recently, we tested a prototype of the Inmodi knee brace in 17 patients from our clinic shortly before total knee arthroplasty (TKA). These patients endured severe osteoarthritis on the leg undergoing surgery and mild to moderate on the contralateral one. A machine learning (ML) algorithm was able to discriminate the leg states with a specificity of 0.96 (perfect=1; data not yet published).

The aim of this pilot project is to further explore the potential of the Inmodi system to diagnose osteoarthritis at earlier stages. Therefore, we will develop a preliminary reference database in a subpopulation at risk of developing osteoarthritis, while following recent recommendations [20]. The identification and validation of novel biomarkers with a ML algorithm require a training dataset and a test dataset, both with potential biomarkers and gold-standard clinical outcomes for validation. This database will require a sample size large enough to be statistically sound to prevent statistical overfitting. Unfortunately, power analysis is not possible for most ML methods, due to the impossibility of guaranteeing statistical assumptions on the distributions of the features and their linear and nonlinear dependencies. That is why we rely on leave-one-subject out nested cross-validation for assessing the statistical relevance of the resulting models. This is the most conservative and robust cross-validation strategy for overfitting. The specific sample size of 120 was considered as feasible within the time constraints of the project.

Noninvasive knee health diagnostics should help identify patients at risk at a relatively low cost and without radiation exposure and enable preventive measures to be implemented earlier than with standard radiographic imaging.

## Methods

### Project Design

This is a prospective, single-center, exploratory study. A cross-sectional and a longitudinal dataset will be collected. A total of 120 participants will be recruited and examined twice at a 9-month interval at the Schulthess Klinik in Zurich (see Table 1 for the measurement procedure). The cross-sectional dataset stems from the first visit of the participants and serves for the identification of AE biomarkers for osteoarthritis. The longitudinal dataset combines the data from the first and second visits and tests whether the osteoarthritis changes can be assessed from the biomarkers. A secondary aim is to evaluate the ability of the AE biomarkers from the first visit to predict the condition’s progression as observed during the second visit.

**Table 1. T1:** Summary table with all project visits, including relevant procedures and timelines.

Study period	Information	Screening	1st visit	2nd visit
Time point	Precall (maximum 2 months)	0	0-2 months	9 months (±2 months)
Oral and written information	✓			
Written consent		✓		
Check inclusion/ exclusion criteria		✓		
Anthropometric and patient data			✓	✓
EOS radiography			✓	✓
MRI^a^			✓	✓
Acoustic emission test with Inmodi knee brace			✓	✓
PROMs^b^ (at home)			✓	✓

a MRI: magnetic resonance imaging.

b PROM: patient reported-outcome measurement.

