### Feature Analysis and Multivariate Modeling

In this stage we will study the association between the extracted parameters and osteoarthritis (using the KL or MOAKS grading as the dependent variable), both individually for each feature and also by creating linear and nonlinear multivariate models. For this, we will follow a strategy guided by the principles of (1) increasing complexity and (2) clinical explainability. Thus, the initial models we consider are linear discriminant analysis and logistic regression, which would be ideal options in case we have a reduced number of highly informative and discriminative features. In this ideal scenario, the models would be highly interpretable and easily translatable to a clinical description. In case more sophisticated models are required, we prioritize ensembles of decision trees, such as random forest and gradient boosting, due to the possibility of performing advanced feature importance analysis and derivation of statistical decision rules.

All features will be tested for normality by Shapiro-Wilk tests and presented as mean (SD; normally distributed data) or median and range and, if needed, in histograms, box plots, or violin plots (nonnormal data).

Associations between AE parameters and osteoarthritis (KL or MOAKS grading) will be evaluated using Pearson (normally distributed data) or Spearman (nonnormal data) repeated measures correlation coefficients, as well as with logistic regression models. Mixed ANOVA will be used to compare differences in the AE, osteoarthritis grading parameters between groups. Also, we will specifically assess the relevance of potential confounding variables such as BMI, age, activity level, and gender. The significance level will be set to *P*=.05, and due to the potentially large number of tests, we will apply the Holm post-hoc correction to all *P* values. For multivariate models, the statistical association will be characterized using leave-one-subject-out nested cross-validation, with a subsequent estimation of a confidence interval for prediction accuracy. This is the most conservative and robust cross-validation strategy for overfitting , and with our sample size (n=120), we will have a good estimation of the model variance. Statistical analyses will be done with R (version 4; R Foundation), Matlab (version 2021b or higher; MathWorks, Inc), and Python (version 3.6 or higher; Python Software Foundation).

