## Discussion

### Principal Findings

This exploratory study aims to identify biomarkers with a prognostic value in the prediction of osteoarthritis. Acoustic, kinematic, and thermal features will be extracted and combined with an artificial intelligence algorithm, and evaluated against gold-standard osteoarthritis diagnosis, such as radiographs and MRI. Some candidate acoustic biomarkers have been identified in a preliminary study [9], using a multifractal analysis method. However, multiple other candidates will be evaluated individually or in combination in our study. Therefore, the primary endpoint can be defined as the area under the curve of the receiver operating characteristic analysis of each biomarker or combination of biomarkers in the regression analysis, finally identifying the parameters with the highest sensitivity and specificity to predict early-stage osteoarthritis in clinical use. AE is patient-dependent, and as such, demographic and baseline health data will be captured and entered as covariates in the regression models. The secondary objective is to evaluate the value of these biomarkers in predicting osteoarthritis evolution. For this objective, the patients will be examined a second time at 9-month intervals, and the new biomarkers will be introduced in regression models to evaluate the predicted performance for osteoarthritis evolution.

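### If used for the longitudinal test, the named repeated measures correlation cannot separate individual tracking from an average visit-to-visit shift present in both sound and osteoarthritis grade

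*Protocol article*

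**What the plan says.** Project Design gives the two-visit data their own purpose: "The longitudinal dataset combines the data from the first and second visits and tests whether the osteoarthritis changes can be assessed from the biomarkers". It names no method there.

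Feature Analysis and Multivariate Modeling says that associations between acoustic parameters and KL or MOAKS grade will be assessed with "Pearson (normally distributed data) or Spearman (nonnormal data) repeated measures correlation coefficients, as well as with logistic regression models". For group comparisons it adds: "Mixed ANOVA will be used to compare differences in the AE, osteoarthritis grading parameters between groups". On adjustment it says "we will specifically assess the relevance of potential confounding variables such as BMI, age, activity level, and gender".

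Principal Findings adds that "demographic and baseline health data will be captured and entered as covariates in the regression models". For the secondary objective, prediction of progression, it says that "the new biomarkers will be introduced in regression models to evaluate the predicted performance for osteoarthritis evolution", without giving the form of those models.

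Visit or time is not named anywhere as a model term or covariate.

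**The concern.** The longitudinal question is whether a knee whose grade changes is also a knee whose sound changes. Repeated measures correlation fits one intercept per person (or knee) and a common slope for sound, and nothing else. Any average movement between visits stays in both variables and enters the statistic as their product.

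Both movements are conceivable here. The sample was chosen for its risk of osteoarthritis, so grades may worsen more often than they improve, and a reading drift between visits would act in the same way. Sound is recorded with airborne microphones, for which the article accepts a lower signal-to-noise ratio. Ambient and device noise have to be separated out, and the participants repeat the same tests nine months later. If both averages move, the study could report that sound follows the disease when it has only seen two unrelated trends. Holm adjustment lowers the rejection rate but does not remove the bias in the coefficient.

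**Working it through.** **Inputs from the article.** Two visits 9 months apart; 120 participants; both knees measured; significance level 0.05; Holm on all P values; 20 participants in Group D booked for knee arthroplasty; people who have knee surgery during follow-up are not invited back. If all Group D operations fall in that period, 120 − 20 = 100 return at most.

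**Assumptions, because the article gives no figures.** The mean shifts and worsening rates below; one knee per person; individual changes in sound and grade independent; unadjusted two-sided 5% test; Pearson form of the statistic.

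**The plan's own figure.** The smallest detectable correlation is tanh[(1.960 + 0.842)/√(120 − 3)] = tanh(0.259) = 0.253. The stated 0.25 reproduces as a two-sided calculation and serves as a yardstick below.

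**Step 1: what the statistic is.** Write dx and dy for the changes in sound and grade. The model grade = person intercept + b × sound gives, with two visits,

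r = Σ dx·dy / √(Σ dx² · Σ dy²), with N − 1 degrees of freedom.

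The means of dx and dy are not subtracted. Adding a visit term subtracts them and gives the ordinary correlation of changes, with N − 2 degrees of freedom. On a test data set of 30 people, the person-intercept model and the through-zero formula both gave 0.1957. The model with visit and the centred correlation both gave 0.1010.

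**Step 2: the spurious correlation.** With unrelated changes and mean shifts m_x and m_y in SD of change, r tends to

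m_x·m_y / √[(1 + m_x²)(1 + m_y²)].

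This is zero if either shift is zero. For equal shifts:
- 0.2 SD: 0.04/1.04 = 0.038
- 0.3 SD: 0.09/1.09 = 0.083
- 0.5 SD: 0.25/1.25 = 0.20

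If a fraction p of knees worsen one grade and none improve, the mean and the mean square of dy both equal p, so r tends to m_x·√p / √(1 + m_x²). At m_x = 0.3 this is 0.091 for p = 0.10 and 0.128 for p = 0.20. The 0.5 SD case comes close to the 0.25 that the plan treats as detectable.

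**Step 3: simulated false-positive rates** (40,000 runs per setting).

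| Setting | N=100, no visit term | N=120, no visit term | With visit term |
|---|---|---|---|
| Sound 0.2 SD, grade 0.2 SD | 7% | 7% | 5% |
| Sound 0.3 SD, grade 0.3 SD | 13% | 15% | 5% |
| Sound 0.5 SD, grade 0.5 SD | 52% | 60% | 5% |
| Sound 0.3 SD, 10% worsen | 14% | 16% | 5% |
| Sound 0.3 SD, 20% worsen | 24% | 28% | 5% |
| Sound 0.5 or 1.0 SD, grade 0 | 5% | 5% | 5% |
| Sound 0, grade 0.5 SD | 5% | 5% | 5% |

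**Step 4: under Holm.** Assume 20 tests, so that the first threshold is 0.05/20 = 0.0025. At N=100 the rejection rate per feature is 1.3% for 0.3 SD in both, 1.5% for 10% worsening and 3.6% for 20% worsening. These are small, but about 5, 6 and 14 times the 0.25% intended. With a visit term the rate is 0.2% to 0.3%.

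**Step 5: both knees pooled per person.** Take four knee-visits per person at N=100, a between-knee grade SD of 0.7, no stable knee difference in sound and a 0.3 SD sound shift. The unadjusted rate is then about 6% with 10% worsening and 11% with 20%.

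**The case against.** **The article does not assign this statistic to the longitudinal test.** Its repeated measures could be the two knees, the mixed ANOVA's within-subject factor is not stated and could be visit, the progression models have no stated form, and the confounder list is introduced as examples. The full plan is not shown. This stands, so the point is conditional. A reader might infer that the longitudinal analysis definitely omits visit, and the article does not establish that. Still, no other named method is described as relating change in sound to change in grade within a person, and the one that does has no visit term by construction.

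**Drift alone is harmless.** A reader might also infer that any shift common to all participants would count as tracking. That is not so: with no mean change in grade, a sound shift of 1.0 SD leaves the error at 5%. Worsening and improvement that balance out (10% each) also leave it at about 5%.

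**The rates are illustrative.** Holm lowers them, pooling knees can lower them, and N=120 may be out of reach. The 0.5 SD case has no support in the document, and at 0.2 SD the inflation is slight. All of this stands.

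**The design limits drift.** Flexion-extension is paced by video, the microphone distance is fixed, device and ambient sounds are to be separated out, and kinematics are recorded. These measures make a sound shift less likely but do not rule it out. They also do nothing about an average change in grade.

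**Conclusion.** The point holds in a limited form. If the repeated measures correlation is used on the two-visit data, it cannot tell individual tracking from average shifts that occur in both sound and grade. At about 100 returning participants, and under the assumptions listed, the unadjusted error runs from 7% at 0.2 SD in both to 52% at 0.5 SD in both, against 5% with a visit term. The article supplies no expected shift, so the true size is unknown and may be small. In an exploratory study this is a cheap improvement on the method named, not a flaw that undermines the study.

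**What to change.** For the longitudinal dataset, state the model as grade = person/knee intercept + visit + b × sound, or equivalently the mean-centred correlation of change in sound with change in grade. Base the tracking claim on b. Report the mean change in each sound feature in group A, who are already measured twice, as a check for drift.

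The cost is one model term, one sentence and one degree of freedom (N − 2 instead of N − 1), with no new data. There is one real downside: if sound and grade truly move together on average because of the disease, that shared movement no longer counts as evidence of tracking. Only differences between knees in how much they change will count.
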